### Trial design

2.2

This study is a multi-center, double-blind, double-dummy, randomized, parallel positive controlled trial. We adopted a noninferiority trial design and followed the Standardized Protocol Interventions: Recommendations for Interventional Trials (SPIRIT) 2013 Statement.^[11]^ The experimental group was treated with HEC and enteric-coated mesalazine tablets (EMT) placebo, while HEC placebo and EMT were used in the control group. A total of 240 patients diagnosed with mild active ulcerative colitis (MAUC) and TCM syndrome of damp-heat stasis blocking and spleen-qi deficiency in 6 clinical trial centers are eligible for enrolment. We will implement randomization with a 1:1 allocation ratio in the experimental group (n = 120) or the control group (n = 120), and each patient will undergo an 8-week treatment. The study flowchart is showed in Figure 1.

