### Eligibility criteria

2.5

Diagnostic criteria:

1.The western medicine diagnostic criteria of UC will refer to Chinese consensus on diagnosis and treatment of IBD (Beijing, 2018).^[14]^2.The TCM diagnostic criteria of the damp-heat stasis blocking and spleen-qi deficiency syndrome will refer to the Clinic terminology of traditional Chinese medical diagnosis and Consensus of traditional Chinese medical in diagnosis and treatment of UC.^[15,16]^ Diagnosis of this syndrome including the main and minor symptoms as following:

Main symptoms:

1.Diarrhea, mucus and bloody stools;2.Abdominal pain;3.Tesmus;4.Tired and lazy;

Minor symptoms:

1.burning anus;2.short and dark-color urine;3.dry and bitter in the mouth;4.drowsiness of limbs;5.poor appetite.

Tongue and pulse: red tongue, thick yellow fur with tooth marks on the sides, and smooth pulse.

Confirmation of the syndrome type: 2 main symptoms (required for the first item) plus 2 minor symptoms, which can be diagnosed by referring to the tongue and pulse.

Inclusion criteria:

1.Diagnosed with active UC.2.Defined by modified Mayo score of 3 to 5 points (mild period).^[14]^3.Differentiation of TCM syndrome is damp-heat stasis blocking accompanied with spleen-qi deficiency.4.Age >18 and <65 years.5.Voluntary to participate and providing written informed consents, as required by Good Clinical Practice.

Exclusion criteria:

1.Patients during remission period, moderate or severe period.2.Pregnancy, lactation, or have desire for pregnancy.3.Severe allergy or allergic to mesalazine or any of the ingredients in HEC.4.Have cardiovascular, pulmonary, liver, renal, endocrine, nerve, and hematology diseases. Blood creatinine level, blood alanine transaminase or aspartate aminotransferase level above the upper limit of normal.5.Have serious complications, such as intestinal stenosis, intestinal obstruction, intestinal perforation, multiple intestinal polyps, toxic megacolon or colorectal cancer, etc.6.Mental disorders or other causes which result in inability of proper expression of feelings.7.Have participated in other medical clinical studies in the last 3 months.8.In addition to mesalazine, receiving other treatments for UC.9.Serious and unstable condition requiring emergency treatment.10.Inappropriate to participate in this trial judged by clinical physicians.

Termination and withdrawal criteria:

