**Table 2 T2:**
[figure not shown]
Modified Mayo score system for assessment of ulcerative colitis activity.

Minor outcomes including individual symptom score, TCM syndrome score, endoscopic response rate, mucosal healing rate, and quality of life scale score.

1.Individual symptom score: referred Guidance Principle of Clinical Study on New Drug of Traditional Chinese Medicine.^[17]^ All symptoms were divided into four levels: none, mild, moderate, and severe. The main symptoms were scored as 0, 2, 4, and 6 points, and the minor symptoms are scored as 0, 1, 2, and 3 points. The tongue and pulse were divided into normal and abnormal grades, 0 and 2 points were recorded in the main symptom, and 0 and 1 points were recorded in the minor symptom.2.TCM syndrome score: The score was graded based on the degree of individual symptom score. All indicators were determined by comparing the values obtained at 2, 4, and 8 weeks with baseline values.Clinical recovery: clinical symptoms disappeared or syndrome score decreased by ≥95% from the baseline;Marked efficacy: the syndrome score decreased by ≥70% and <95% compared with the baseline;Efficacy: the syndrome score was a decrease of at least 30% and less than 70% from the baseline;Invalid: the syndrome score was a decrease of less than 30% from the baseline;Worsen: the syndrome score exceeded the baseline after treatment.TCM syndrome efficacy rate = (Clinical recovery + Marked efficacy + Efficacy) cases /a total number of cases ×100%.Endoscopic response rate: was defined as endoscopic score decreased at least 1 point from the baseline in the modified Mayo score. Endoscopic response rate = endoscopic response cases / total number of the group ×100%.(2)Mucosal healing rate: was defined as absolute subscore for endoscopy of 0 or 1. Mucosal healing rate = Mucosal healing cases / total number of the group ×100%.(3)Quality of life assessment: Patients were evaluated by Inflammatory Bowel Disease Questionnaire,^[18]^ included the 32 most frequent and important items. Inflammatory Bowel Disease Questionnaire was divided into 4 modules: bowel symptoms (10 questions), systemic symptoms (5 questions), emotional function (12 questions), and social function (5 questions). Each question has graded responses from 1 to 7, and thus the total score is ranging from 32 to 224, with higher scores representing a better quality of life.

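### Mucosal healing has no baseline condition, so a patient who enters with an endoscopy subscore of 0 or 1 and does not change is counted as healed

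*Protocol article*

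**What the plan says.** Section 3.4 (Outcomes) sets the criterion: "Mucosal healing rate: was defined as absolute subscore for endoscopy of 0 or 1". No fall from baseline is asked for. The denominator is the whole arm: "Mucosal healing rate = Mucosal healing cases / total number of the group ×100".

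The other endoscopic outcome in the same list, endoscopic response, is based on change: it "was defined as endoscopic score decreased at least 1 point from the baseline in the modified Mayo score". Both are secondary: "Minor outcomes including individual symptom score, TCM syndrome score, endoscopic response rate, mucosal healing rate, and quality of life scale score".

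Section 2.5 (Eligibility criteria) fixes severity at entry by the total score alone: "Defined by modified Mayo score of 3 to 5 points (mild period". The matching exclusion is "Patients during remission period, moderate or severe period", which adds no endoscopic threshold. The TCM syndrome must also be confirmed by "2 main symptoms (required for the first item) plus 2 minor symptoms"; the first item is diarrhea with mucus and bloody stools. Some of the 3 to 5 points will therefore usually come from symptoms.

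**The concern.** An endpoint called healing should count patients who had something to heal. Here the criterion is a level that can already be met on the day of enrolment, in a population selected for mild disease, and nobody is removed from the denominator for meeting it. One patient who enters at endoscopy 1 and is still at 1 at week 8 is a non-responder on one endoscopic outcome and healed on the other.

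The result would be hard to read in two ways. The rate in each arm would mix a treatment effect with the make-up of the enrolled sample. The difference between arms would also be pulled toward zero. Section 2.2 says "We adopted a noninferiority trial design", and in that setting similar rates are welcome, so readers may take an insensitive endpoint as support. The Discussion names the lack of enteroscopy as a shortcoming of the earlier HEC trial, so the endoscopic outcomes will be looked at closely.

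**Working it through.** The article states no figure for mucosal healing, so there is none to reproduce. The sample size in section 2.3 rests on efficacy rates and has no bearing here.

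**Step 1. Can a patient meet the criterion at entry?** The inputs are healing = endoscopy 0 or 1, denominator = whole group (both section 3.4), and entry = total 3 to 5 with no endoscopic minimum (section 2.5). Nothing in these rules keeps out a patient at endoscopy 0 or 1. If the score has four items of 0 to 3, a patient scoring 1 + 1 + 1 + 1 = 4 qualifies and already meets the criterion.

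**Step 2. How much of the admissible score space is affected?** Under the same assumption, list every combination with total 3, 4 or 5:

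| Total | Patterns | Endoscopy 0 | 1 | 2 | 3 | Share at 0 or 1 |
|---|---|---|---|---|---|---|
| 3 | 20 | 10 | 6 | 3 | 1 | 16/20 = 80% |
| 4 | 31 | 12 | 10 | 6 | 3 | 22/31 = 71% |
| 5 | 40 | 12 | 12 | 10 | 6 | 24/40 = 60% |
| All | 91 | 34 | 28 | 19 | 10 | 62/91 = 68% |

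The share under other assumptions:
- endoscopy at least 1: 28/57 = 49%
- stool frequency and bleeding each at least 1: 27/32 = 84%
- stool frequency, bleeding and endoscopy each at least 1: 10/15 = 67%
- a three-item score: 19/34 = 56%

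These are shares of possible patterns, each counted once. They are not shares of patients. They show that the problem is not confined to a rare corner of the entry range.

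**Step 3. Effect on the rates.** Let s be the share entering at 0 or 1 and staying there, and h the healing rate among those entering at 2 or more.

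- Reported rate in an arm = s + (1 − s)h, which is never below s.
- Reported difference = (1 − s)(h₁ − h₂) = (1 − s)D.

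The value of s is not in the article. For an assumed range of 30% to 60% and D = 20 points, the reported difference is 0.7 × 20 = 14 points down to 0.4 × 20 = 8 points.

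A worked case with assumed h of 50% and 35% (D = 15 points):

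| s | Rate 1 | Rate 2 | Difference |
|---|---|---|---|
| 0 | 50% | 35% | 15 points |
| 0.2 | 60% | 48% | 12 points |
| 0.4 | 70% | 61% | 9 points |
| 0.6 | 80% | 74% | 6 points |

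**Step 4. What restricting the denominator costs.** Of 120 per arm, 120 × (1 − s) remain: 84 at s = 0.3 and 48 at s = 0.6. In the worked case at s = 0.6:

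- Whole group: standard error √[(0.80 × 0.20 + 0.74 × 0.26)/120] = 5.4 points, for a difference of 6. Ratio 1.1.
- Restricted: standard error √[(0.50 × 0.50 + 0.35 × 0.65)/48] = 10.0 points, for a difference of 15. Ratio 1.5.

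The restricted estimate is less precise, but in this case the difference is larger relative to its error.

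**The case against.** **The size is unknown.** A reader might infer that many enrolled patients will already count as healed. The documents do not support that. No baseline endoscopy distribution is given, Table 2 is not shown, and the item structure is assumed. Of the 62 patterns, 34 have endoscopy 0, which may be uncommon in patients diagnosed with active UC. The diagnosis follows a cited consensus that cannot be checked here and might require visible activity. This stands, and it is why the 28 of 57 count is given beside 62 of 91. It does not rescue the definition: a requirement of at least 1 would still admit patients at exactly 1.

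**The comparison is not biased toward one arm.** A reader might infer that the definition favours HEC or produces a false non-inferiority finding. Allocation is randomised and stratified by centre, so the share at 0 or 1 is the same in both arms in expectation. The article attaches no margin to this outcome, and section 3.7 plans chi-square or Fisher tests for a difference. What remains is loss of sensitivity.

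**Not everyone at 0 or 1 will stay there.** Section 2.5 foresees patients whose symptoms worsen. If the two arms keep shares r₁ and r₂ of these patients at 0 or 1, the difference becomes s(r₁ − r₂) + (1 − s)D, so staying low carries some information. That is maintenance of a low score, however, and not healing.

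**The threshold itself.** A reader might conclude that healing should mean subscore 0. That does not follow. The fault is the missing baseline condition; under a cut-off of 0, patients entering at 0 would still count as healed without change.

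**A companion endpoint exists.** Endoscopic response needs a fall of at least 1 point, so an unchanged patient cannot meet it. This limits the damage and keeps the point minor.

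**Conclusion.** The point holds as a modest flaw in a secondary outcome. From the text alone, a patient entering at endoscopy 0 or 1 and unchanged at week 8 is counted as healed, as is one who worsens from 0 to 1, and no other section repairs this. The size cannot be fixed from the article. It depends on s, for which the pattern counts are only a rough indication and rest on an assumed four-item 0 to 3 score. Given s, and provided those patients stay at 0 or 1, the floor is s in both arms and the difference shrinks by the factor 1 − s. The primary outcome definitions and the sample size are untouched by this point.

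**What to change.** In section 3.4, keep the criterion of endoscopy subscore 0 or 1 at week 8, but compute the mucosal healing rate only among patients whose baseline endoscopy subscore is at least 2. Report the distribution of the baseline endoscopy subscore by arm, so that readers can see how many patients were left out and whether the arms are alike. Keep endoscopic response as it is. Leave the threshold at 0 or 1.

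The change uses scores already collected and needs no extra visits or patients. It should be fixed before unblinding. The cost is a smaller denominator, for example 84 or 48 per arm if 30% or 60% enter at 0 or 1 (assumed shares), and with it a wider interval for this secondary outcome.

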### Safety assessment

3.5

Adverse events (AEs) will be documented and assessed by the local principal investigators during this trial, including clinical signs, symptoms, and laboratory tests. All patients will undergo the following laboratory texts between the start and end of the trial. The safety assessment indices included blood pressure, respiration rate, heart rate, body temperature, and physical examination in addition to blood routine examination, urine routine test, stool routine examination and occult blood, liver function tests (AST, ALT, TBIL, DBIL, γ-GT, ALP), kidney function tests (Scr, BUN) and electrocardiogram. Any AEs will be requested to record in electronic CRFs (eCRFs) regardless of their relationship to the intervention. Severe AEs will be stopped immediately and reported to the local drug administration authorities within 24 hours including a detailed description of the time, severity, possible relationship with the drug, and the treatment measurement will be recorded.

### Data management and quality control

3.6

The quality assessment of the trial will be conducted in the following aspects: the CRFs, patient diary card, original laboratory examination, informed consent, and drug distribution and storage. The trial information of patient will be recorded in CRFs by a trained and qualified investigator, and the completed CRF will not be allowed to any corrections. The CRFs of each center will be reviewed regularly by clinical inspectors for data quality inspection. The investigators will input and manage the electronic CRFs (eCRFs) online through the Clinical data management system (eCDMS3.0) of Xiyuan Hospital, China Academy of Chinese Medical Sciences. Data input was repeated by 2 investigators to ensure the data accuracy. In addition, all paper documents will be preserved in the Jiangsu Provincial Hospital of Chinese Medicine for 5 years after trial completing and only can be viewed by the research team. Besides, all the datasets will be conducted and monitored by Guangzhou Hipower Pharmaceutical R&D Co, Ltd, which acted as Composition of data monitoring committee of this trial. It will audit the trial conduct and datasets every week.

### Data analysis

3.7

Data analysis will be performed by professional statisticians and the main researchers using SPSS 22.0. Statistical analysis included the actual number of subjects selected, cases of shedding and rejection, demography and other baseline characteristics, patient compliance, efficacy and safety analysis. We used frequency tables or percentages for categorical variables, and mean ± standard deviation for continuous variables to describe the characteristics of patients in both groups. Categorical data will be analyzed by chi-square test or Fisher exact test to compare the differences between the 2 groups, while quantitative data with normal distribution will be analyzed by *t* test. If the data does not conform to the normal distribution or the uniformity of variance, Wilcoxon rank sum test or Wilcoxon signed test will be used to analyze them to compare the two groups. A two-sided *P-*value <.05 will be set as the significant level.

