### Number of Samples

2.3

Number of Samples was determined based on the calculation of noninferiority trial design. The efficacy rates of EMT ranges from 65% to 71%,^[12,13]^ and the average rate is about 68%. Our previous study found that the efficacy rates of HEC is 83.11% in treating MAUC. The sample size was calculated by the following formula: 

*U*α, *U*β is the corresponding *U* value of α, β. When α equaling to 0.05, β equaling to 0.1, *U*α (0.05) is 1.645, *U*β (0.2) is 0.842. *P*_1_ and *P*_2_ represent the efficacy rates of HEC and EMT. *P* equals to (*P*_1_ + *P*_2_) /2 × 100%. The certainty was set at 80%, considering 20% of sample lose. The sample number was set to 120 for each group, 240 in total, and 40 samples in each center.

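### The design is declared noninferiority, but the only stated test for the primary rates is a two-sided test of a difference with no margin, so a non-significant result would leave the trial's question unanswered

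*Protocol article*

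**What the plan says.** All references are to the protocol article.

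- Section 2.2 (Trial design): "We adopted a noninferiority trial design".
- Section 2.3 (Number of Samples): "Number of Samples was determined based on the calculation of noninferiority trial design". The symbols explained there are two normal quantiles, the average rate P, and P1 and P2, which "represent the efficacy rates of HEC and EMT". None is a margin. The values given are 83.11% for HEC, 68% for EMT, quantiles 1.645 and 0.842, 80% power, 20% loss, and 120 per group.
- Section 3.4 (Outcomes): the primary outcomes are two rates at week 8, clinical efficacy and clinical remission.
- Section 3.7 (Data analysis): "Categorical data will be analyzed by chi-square test or Fisher exact test to compare the differences between the 2 groups". The rule for significance is a two-sided P "value <.05 will be set as the significant level". No noninferiority hypothesis and no confidence-limit rule is given.
- Section 4 (Discussion) expects the results to bear on whether HEC can replace mesalazine or lower its use.

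**The concern.** A chi-square or Fisher test takes as its null hypothesis that the two rates are equal. A noninferiority analysis takes as its null that HEC is worse than EMT by at least a stated margin. The two can give opposite answers on the same data. Failing to reject equality may mean only that the trial is too small to see a real deficit. Rejecting equality against HEC says nothing about whether the deficit is tolerable unless a margin has been fixed.

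The primary conclusion is at stake. A noninferiority design is meant for the case where the new treatment is about as good as the standard one. In that case the stated test will usually be non-significant, and the plan gives no rule for what follows. Reading that result as showing HEC to be as good as mesalazine would be easy and wrong, and it would bear directly on the substitution claim in the discussion.

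**Working it through.** **1. Where the 120 comes from.** The printed formula did not survive extraction, so I rebuilt it from the symbols that section 2.3 defines: n = 2P(1−P)(Uα+Uβ)²/(P1−P2)².

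- P = (0.8311 + 0.68)/2 = 0.75555, so 2P(1−P) = 0.36939.
- (1.645 + 0.842)² = 6.1852.
- (0.8311 − 0.68)² = 0.022831.
- n = 0.36939 × 6.1852/0.022831 = 100.07 per group. Multiplied by 1.2 for loss, this is 120.08.

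This matches the stated 120. It is a one-sided 0.05, 80% power calculation for showing a difference, with no margin term. Two details of section 2.3 also need tidying: β is first given as 0.1 but the quantile used is that for 0.2, and 1.645 is one-sided while section 3.7 tests two-sided.

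One noninferiority reading also gives 120: a 15-point margin, equal rates of 68%, one-sided 0.05, 80% power. That 120 is before any loss (150 after it), and it does not use the 83.11%. It does not fit the stated inputs.

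**2. What the stated test does.** I enumerated the binomial outcomes exactly, using the uncorrected chi-square at two-sided 0.05 and a 68% EMT rate. The arm sizes are 120, and 96 (120 less the planned 20%). The 10- and 15-point deficits are assumptions chosen for illustration.

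| True HEC rate | Result | 96 per arm | 120 per arm |
|---|---|---|---|
| 83.11% | significant, favours HEC | 69% | 79% |
| 68% | significant, favours HEC | about 2.5% | about 2.5% |
| 68% | not significant | about 95% | about 95% |
| 58% (10 points worse) | not significant | 70.3% | 63.2% |
| 53% (15 points worse) | not significant | 43.8% | 32.7% |

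**3. An example.** With 96 per arm, take 55 HEC and 65 EMT responders. The difference is 57.3% − 67.7% = −10.4 points, p = 0.14. The standard error is √(0.573×0.427/96 + 0.677×0.323/96) = 0.0695, so the 95% interval is −10.4 ± 1.96 × 6.95, or −24.0 to +3.2 points. The test finds no significant difference, yet the data are compatible with a 24-point loss.

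**4. Power once a margin is set.** No document gives a margin, so 10 and 15 points are assumptions. With both rates at 68%, SE = √(2×0.68×0.32/n), and power = Φ(margin/SE − 1.96).

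- 96 per arm, SE 0.0673: 10 points gives Φ(−0.47) = 32%; 15 points gives Φ(0.27) = 61%.
- 120 per arm, SE 0.0602: 10 points gives Φ(−0.30) = 38%; 15 points gives Φ(0.53) = 70%.

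If HEC truly reaches 83.11%, power exceeds 98% for either margin, even with 96 per arm. The adequacy of 120 per group therefore depends on how much better than EMT HEC is assumed to be.

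**The case against.** Three stronger readings are tempting, and the document does not support them.

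- **That the trial has no route at all to its claim.** A two-sided P below 0.05 in favour of HEC shows superiority, and superiority implies noninferiority for any positive margin. Under the planning rates that result has a probability of about 69% to 79%. This stands. The gap is confined to the case where HEC is similar to EMT or somewhat worse.
- **That the plan will treat P > 0.05 as noninferiority.** No section says so. The 70% and 63% figures are error rates only if someone reads the result that way.
- **That no margin exists anywhere.** This is a condensed article, the formula image is lost, and an unseen full protocol or SAP could hold a margin. Silence on the margin alone would not be a finding.

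It can also be said that section 3.7 is a general paragraph that never names the primary outcome, so a separate noninferiority test may sit elsewhere. That is possible. Still, section 3.7 states a rule for categorical data, the primary outcomes are rates, and no exception is made. The conflict lies between what sections 2.2 and 2.3 declare and what section 3.7 states, and an unseen document does not remove it from this text.

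**Conclusion.** The point holds in this form: the stated test does not match the declared design. The article gives no margin, and the sample size behaves like a superiority calculation. If the true rates are equal at 68%, the stated analysis can lead to a noninferiority conclusion only through a chance significant result, about 2.5% of the time; about 95% of trials would end non-significant, with no rule for interpreting them.

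The figures assume a 68% EMT rate, an uncorrected chi-square, and 96 or 120 evaluable per arm. The deficits and margins are illustrative. That the lost formula has no margin is a strong inference from the symbol list and the reproduced 120, not a certainty. The mismatch governs the primary conclusion, so it should be resolved before unblinding.

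**What to change.** Choose one of two routes before unblinding, and make sections 2.2, 2.3 and 3.7 agree.

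1. **Keep noninferiority.** State a margin for the difference in the week-8 rate and justify it. Conclude noninferiority only if the lower limit of the two-sided 95% confidence interval for HEC minus EMT lies above minus the margin. Test superiority only after that. Restate the power at 120 per group for the chosen margin, both at the planning rates and at equal rates.
2. **Redeclare the trial as superiority.** This matches the stated test and the sample-size arithmetic. Restate the power under the two-sided test: about 69% with 96 per arm and 79% with 120, against the 80% planned.

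Under either route, add a sentence that a non-significant difference test is not evidence of noninferiority.

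The change of wording needs no new data. The first route commits the sponsor to a margin and may show that 120 per group is too few unless HEC is truly better than EMT. The second gives up a noninferiority claim if superiority is not shown.
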